## Abstract

**Background::**

Patients with coronary heart disease (CHD) angina pectoris are in critical condition, which can cause sudden death, myocardial infarction, and other adverse events, and bring serious burden to families and society. Timely treatment should be given to improve the condition. Western medicine treatment of angina pectoris failed to meet the demand of angina symptom control.

**Objective::**

It is hoped that the research method with higher evidential value will be adopted to compare the short-term, medium-term, and long-term effects of Chinese patent medicine combined with conventional western medicine and conventional western medicine alone in the treatment of CHD angina pectoris, so as to tap the clinical efficacy advantages of traditional Chinese medicine (TCM) and provide reliable data support for its clinical application.

**Methods::**

A prospective cohort study was conducted among patients with CHD angina pectoris who were treated with oral Chinese patent medicine and conventional western medicine. The patients were divided into exposed group and nonexposed group according to whether or not the patients with CHD angina pectoris were treated with Chinese patent medicine. The exposed group was treated with TCM combined with conventional western medicine, while the nonexposed group was treated with conventional western medicine alone. Patients need to be hospitalized for 2 weeks as the introduction period and whether to enter the group is determined according to the treatment and medication conditions of the patients. The follow-up time points were 0th, 4th, 12th, 24th, and 48th weeks. The main events and secondary events were used as the evaluation criteria for clinical efficacy of CHD angina pectoris. In the experimental study, we will use strict indicators to detect standard operation procedure for multinomics and bacterial flora detection.

**Conclusion::**

This study will provide evidence for the clinical efficacy advantages of Chinese patent medicine and reliable support for its clinical application through test data.

## Introduction

1

Coronary heart disease (CHD) is a heart disease caused by myocardial ischemia and hypoxia due to coronary atherosclerosis. Angina pectoris is closely related to coronary artery insufficiency and is common in clinical practice.^[1,2,3]^ Patients with CHD angina pectoris are in critical condition, which can cause sudden death, myocardial infarction, and other adverse events, and bring serious burden to families and society. Timely treatment should be given to improve the condition.^[2,3,4,5]^ Clinical attention has long been paid to the treatment of CHD angina pectoris. Western medicine for angina pectoris mainly uses β-receptor blocker, calcium channel blocker, angiotensin converting enzyme inhibitor, angiotensin II receptor antagonist, etc.^[6]^ It has good clinical effect, but the demand for angina symptom control is still unsatisfied.^[7]^

As a unique medical resource in China, traditional Chinese medicine (TCM) plays an important role in disease treatment and health services. Chinese patent medicine is made of Chinese herbal medicines as raw materials and processed into various dosage forms of Chinese traditional medicine products, including pills, powders, granules, pastes, capsules, Chinese traditional medicine injections, aerosols, etc. Its advantages are ready availability, adaptability to urgent need, convenient storage, easy carrying, and saving decocting process, etc, and eliminating peculiar smell and adverse stimulation when taking TCM decoction.^[8,9,10]^ According to statistics, the number of Chinese patent medicines in the 2012 edition of the basic medicine catalog has increased to 203, accounting for 39%, of which 23 are Chinese patent medicines for the treatment of cardiovascular diseases.^[11]^ Eight kinds of commonly used cardiovascular Chinese patent medicines and 28 kinds of antiangina Chinese patent medicines are included in New Pharmacology.^[12]^ In recent years, many studies have shown that Chinese patent medicine has achieved certain curative effect in the dialectical treatment of angina pectoris, which has the advantages of good effect and few adverse reactions.^[13,14,15,16,17]^ However, Chinese patent medicine is difficult to match western medicine with large-scale clinical trials in treatment, health education, and publicity. Therefore, a research method with higher evidence value-clinical cohort study is needed to conduct evidence-based research on it.

The results of cohort study belong to class II evidence-based medicine, and its research evidence is second only to randomized controlled trials (RCTs). However, cohort study has its advantages such as long time, large sample, and so on. Cohort study design can follow the characteristics of individualized diagnosis and treatment of TCM and dynamic changes of treatment schemes, and take Chinese patent medicine as a factor to comprehensively evaluate the curative effect of Chinese patent medicine on CHD angina pectoris.^[18]^ In this study, prospective cohort study was used to study the clinical efficacy of Chinese patent medicine in the adjuvant treatment of CHD angina pectoris, so as to enrich the evidence of efficacy evaluation of Chinese medicine. Establish innovative methods and techniques for the evaluation of clinical efficacy of TCM, and then promote its deeper research and application.

## Method

2

A prospective cohort study was conducted among patients with CHD angina pectoris who were treated with oral Chinese patent medicine and conventional western medicine. The patients were divided into exposed group and nonexposed group according to whether or not the patients with CHD angina pectoris were treated with Chinese patent medicine. The exposed group was treated with TCM combined with conventional western medicine, while the nonexposed group was treated with conventional western medicine alone. Patients need to be hospitalized for 2 weeks as the introduction period and whether to enter the group is determined according to the treatment and medication conditions of the patients. The follow-up time points were 0th, 4th, 12th, 24th, and 48th weeks. The main events, secondary events and adverse events were used as the evaluation criteria for clinical efficacy of CHD angina pectoris. In the experimental study, we will use strict indicators to detect standard operation procedure for multigroup and bacteria detection. It is hoped that the research method with higher evidential value will be adopted to compare the short-term, medium-term, and long-term effects of Chinese patent medicine combined with conventional western medicine and conventional western medicine alone in the treatment of CHD angina pectoris, so as to tap the clinical efficacy advantages of TCM and provide reliable data support for its clinical application. The technical route is shown in Figure 1.

**Figure 1 F1:**
[figure not shown]
Prospective cohort study of Chinese medicine in the treatment of coronary heart disease (CHD) angina pectoris. TCM = traditional Chinese medicine.

### Qualified research subject

2.2

#### Diagnostic criteria of western medicine

2.2.1

Diagnostic criteria for CHD angina pectoris: According to the guidelines for the diagnosis of CHD angina pectoris formulated by the American Heart Association and the Heart Association (ACC/AHA) in the Guidelines for the Treatment of Chronic Stable Angina Pectoris (2007) and the Guidelines for the Management of Patients with Unstable Angina Pectoris and Non-ST-Elevation Myocardial Infarction (2011), and referring to the Guidelines for the Diagnosis and Treatment of Chronic Stable Angina Pectoris in China in 2007, and the Guidelines for the Diagnosis and Treatment of Unstable Angina Pectoris and Non-ST-Elevation Myocardial Infarction in China in 2007, diagnostic criteria are formulated by Chinese Society of Cardiology, Chinese Journal of Cardiology. And the Chinese Medicine Research Association of China and Western Medicine combined with the Cardiovascular Disease Prevention and Rehabilitation Committee established the Standard for the Consensus of Integrative Medicine for Integrative Medicine for the Treatment of Coronary Heart Disease (2019).

Diagnosis can be made by meeting any one or more of the following:

1.The definite history of old myocardial infarction.2.Coronary angiography or computed tomography angiography examination showed that the diameter of at least 1 main branch of coronary artery was ≥50%.3.Patients with ST-segment depression or T-wave inversion after coronary revascularization (percutaneous transluminal coronary intervention [PCI] or coronary artery bypass grafting [CABG]).

The diagnosis of unstable angina pectoris of CHD refers to the Guidelines for Diagnosis and Treatment of Unstable Angina Pectoris and Non-ST-Segment Elevation Myocardial Infarction issued by Chinese Society of Cardiology and Chinese Journal of Cardiology in 2007, including the following subtypes:

1.Resting angina pectoris: Angina pectoris attack at rest, and the duration is usually more than 20 minutes.2.Initial angina pectoris: New angina pectoris occurred within 1 month, which may be characterized by spontaneous and exertional episodes, with pain ranking above grade III.3.Aggravated exertional angina pectoris: Previous history of angina pectoris, aggravation of angina pectoris in the past month, frequent attacks, prolonged time or reduced pain closure (angina pectoris grade at least increased by grade I, or at least reached grade III).4.Variant angina pectoris: Usually spontaneous. It is characterized by transient ST segment elevation, most of which spontaneously relieves and does not develop into myocardial infarction, but a few of which can develop into myocardial infarction. Atherosclerotic plaque leads to local endothelial dysfunction and coronary artery spasm, which are the causes of the disease. Nitroglycerin and calcium antagonist can relieve it.

#### Criteria for differentiation of symptoms and signs in TCM

2.2.2

The TCM syndrome differentiation reference standard refers to the 2002 edition of the Guiding Principles for Clinical Research of TCM (New Drugs), the internal medicine of TCM (the 7th edition of teaching materials), and the revision of the consensus of experts in TCM diagnosis and treatment of chest pain after PCI in 2014.

#### Inclusion criteria

2.2.3

The inclusion criteria were as follows:

1.Voluntary participation, understanding, and signing of informed consent form.2.The age ranged from 35 to 75 years old and gender is not limited.3.For patients with angina pectoris of CHD in the inpatient department or outpatient department of cardiology, the diagnosis of angina pectoris conforms to the relevant guidelines issued by ACC/AHA, Chinese Society of Cardiology and Chinese Journal of Cardiology.4.For patients who meet the standard of drug therapy, the exposed group is treated with Chinese patent medicine combined with conventional western medicine, while the nonexposed group is treated with conventional western medicine alone.

#### Exclusion criteria

2.2.4

The exclusion criteria were as follows:

1.Patients who are combined with other cardiac diseases, neurosis, climacteric syndrome, hyperthyroidism, cervical spondylosis of spinal cord or vertebral artery type, gastroesophageal reflux disease or hiatal hernia, and other diseases that may cause chest pain.2.Angina pectoris patients with serious and uncontrollable symptoms, suffering from acute myocardial infarction, heart failure, myocarditis, cardiomyopathy, severe heart valve diseases, liver failure or renal failure, malignant tumor, severe metabolic diseases, and other major diseases.3.Women who are pregnant or lactating or women are in childbearing age with fertility requirements.4.Patients with a mental disorder or cognitive dysfunction.5.Patients who have participated in other trials within the past 3 months.6.Patients with a history of allergy or with a known allergy to the study drug.7.Patients who are expected to poor compliance and unpossible regular visits.8.Patients with no current address or incomplete current address without contact telephone number.9.Patients who are unable to participate in the study, as judged by the investigator.

### Sample size calculation

2.3

The sample size calculation formula is shown in Figure 2. The expected incidence rates of exposed group and nonexposed group were obtained through literature review,^[18,19]^
*P*
_1_ = 0.072, *P*
_0_ = 0.059, *q* = 1 − *p*, *Z*
_*α*_ and *Z*
_*β*_ were the areas under the standard normal distribution, and the table was found to obtain *Z*
_*α*_ = 2.58, *Z*
_*β*_ = 1.64. Substituting the above values into the formula can be obtained, and the sample size of each group is about 5677 cases. Control the rate of loss of follow-up within 10%, mainly to ensure a certain professional representation. There were about 6200 cases in each group, and the total sample size of this study was about 12,400.

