#### Evaluation criteria for clinical efficacy of CHD angina pectoris

2.8.4

1.Main events: The incidence of cardiovascular events includes acute myocardial infarction, PCI or CABG.2.Secondary events(a)All causes of death.(b)Readmission due to cardiovascular events.(c)Seattle Angina Questionnaire (SAQ): The degree of pain in angina pectoris, the frequency and duration of acute paroxysmal angina pectoris, etc.(d)Routine admission examination: Carotid artery color Doppler ultrasound, cardiac color Doppler ultrasound, electrocardiogram, transcranial color Doppler ultrasound, chest radiograph, and other imaging examinations; Clinical biochemical tests such as troponin, brain natriuretic peptide, emergency 7 items, myocardial enzyme, D-dimer, coagulation four items, hematuria and stool routine, etc.3.Adverse events:(a)Produce toxic reactions (such as severe gastrointestinal reactions, gingival bleeding, etc).(b)Anaphylactic shock.(c)Liver and kidney function damage caused by TCM.

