#### Main statistical analysis methods

2.11.2

Descriptive analysis and inferential analysis of clinical features before and after treatment were as follows:

1.Metrologic data: Comparative analysis before and after treatment between groups or within groups. First, normal test is carried out on the distribution of variables.(a)When obeying normal distribution, statistical description is expressed by mean number, standard deviation, number of cases, minimum value and maximum value, etc. Statistical method is *t* test or variance analysis.(b)Nonnormal distribution. Statistical description is expressed by median, upper quartile (Q1), lower quartile (Q3), 95% confidence interval, etc. Statistical method is analyzed by rank sum test (Wilcoxon method).(c)If the influence of the center or other factors is considered, covariance analysis is used.2.Counting data: Descriptive statistical analysis is made by frequency table, percentage, or composition ratio. Comparative analysis before and after intra-group or intra-group treatment was performed by Chi-squared test and Fisher exact probability method. At the same time, relative risk was calculated to illustrate the correlation strength between exposure and outcome.3.Grade data: Rank sum test (Mann–Whitney method) was used for comparison between groups.4.Analysis of influencing factors of curative effect: Regression analysis is adopted, including age, sex, treatment, and other factors that may affect the judgment of curative effect.5.The incidence rate and median time of cardiovascular events were analyzed by Kaplan–Meier method, and Cox regression analysis was used to process truncated data of cardiovascular events caused by missed visits.6.Stratified analysis: Compare the stratified curative effects by drug usage and drug treatment duration. Baseline comparison test level *α* = 0.05, and efficacy comparison test level *α* = 0.05 between groups. General statistical tests adopt bilateral tests, and those with *P* <.05 are considered to have statistical significance.

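### As printed, the planning rates give the Chinese patent medicine group the higher rate of cardiovascular events, against the study's stated aim; each rate must be labelled by group and outcome

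*Protocol article*

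**What the plan says.** Section 2.3 (Sample size calculation) introduces the two planning rates with "The expected incidence rates of exposed group and nonexposed group were obtained through literature review" and lists P1 = 0.072, P0 = 0.059, Zα = 2.58 and Zβ = 1.64. It concludes that "the sample size of each group is about 5677 cases", raised to about 6200 per group and 12,400 in total with loss to follow-up held within 10%. It names neither the event nor the time window for the rates.

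Section 2 (Method) defines exposure: "The exposed group was treated with TCM combined with conventional western medicine, while the nonexposed group was treated with conventional western medicine alone". Section 2.8.4 gives the main outcome: "Main events: The incidence of cardiovascular events includes acute myocardial infarction, PCI or CABG". The Method section states the purpose of the comparison: "so as to tap the clinical efficacy advantages of TCM and provide reliable data support for its clinical application". Section 2.11.2 sets "efficacy comparison test level *α* = 0.05 between groups" and adds that "General statistical tests adopt bilateral tests".

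**The concern.** Section 2.3 names the exposed group first and the nonexposed group second, then gives P1 before P0. In cohort notation, subscript 1 normally means exposed and 0 nonexposed. Both cues assign 7.2% to patients taking Chinese patent medicine and 5.9% to those on western medicine alone. Every component of the main outcome is unfavourable, so a higher incidence is worse. Read as printed, the design assumes that adding Chinese patent medicine raises the rate of infarction and revascularisation, while the objective is to show that it helps. Nothing in the available text explains or reverses that direction.

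The assumed effect is one of the inputs behind 12,400 patients, and the result will later be judged against it. If the labels are merely reversed, the text is wrong but the number stands. If 5.9% really is the rate on western medicine alone, the benefit the study is meant to detect has not been stated, and neither has its power for that benefit. If the rates come from another outcome or population, the planning basis itself is in doubt.

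**Working it through.** **Inputs from the protocol article.** P1 = 0.072, P0 = 0.059, printed Z values 2.58 and 1.64, 5677 per group before loss, 6200 per group after allowance for loss (section 2.3); two-sided tests at alpha 0.05 (section 2.11.2). The protocol's own formula is in Figure 2, which is not available here, so I used the standard two-proportion formula with equal groups:

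n = [Zα·√(2p̄(1−p̄)) + Zβ·√(p1(1−p1) + p0(1−p0))]² / (p1 − p0)², with p̄ the mean of the two rates.

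**1. Direction as printed.** Risk ratio 0.072/0.059 = 1.22; difference 0.072 − 0.059 = +0.013, or 1.3 points more events in the exposed group.

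**2. Reproducing 5677.** p̄ = 0.0655, √(2 × 0.0655 × 0.9345) = 0.34988, √(0.072 × 0.928 + 0.059 × 0.941) = 0.34976.
- Z = 1.96 and 0.84 (two-sided alpha 0.05, 80% power): (1.96 × 0.34988 + 0.84 × 0.34976)² / 0.013² = 5678. This matches the stated figure.
- Printed Z = 2.58 and 1.64: (2.58 × 0.34988 + 1.64 × 0.34976)² / 0.013² = 12,897, or about 12,900. This does not match.

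So 0.072 and 0.059 are the rates behind the sample size, but the printed Z values are not. The steps below use alpha 0.05 and 80% power.

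**3. Swapping the labels.** Exposed 0.059, nonexposed 0.072: risk ratio 0.059/0.072 = 0.82. The formula depends only on p̄, the sum of the two variances and the squared difference. All are unchanged, so n is again 5678.

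**4. If the rates are true as labelled.** With 5677 per group, the standard error of the difference is √[(0.072 × 0.928 + 0.059 × 0.941)/5677] = 0.00464, and 0.013/0.00464 = 2.80. The chance of a significant excess in the exposed group is about 80%. The chance of a significant result in its favour is Φ(−1.96 − 2.80), about 1 in a million.

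**5. If 0.059 is truly the nonexposed rate and a benefit is sought.** The article gives no exposed rate for this case, so two natural assumptions are shown. Evaluable patients after 10% loss: 6200 × 0.90 = 5580 per group. Power = Φ{[√5580·|p1 − p0| − 1.96·√(2p̄(1−p̄))] / √(p1(1−p1) + p0(1−p0))}.

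| Assumed benefit | Exposed rate | n per group for 80% power | Power at 5580 |
|---|---|---|---|
| Inverse risk ratio, 0.82 | 0.059 × 0.059/0.072 = 0.04835 | 7025 | 70% |
| Same absolute difference, 1.3 points | 0.059 − 0.013 = 0.046 | 4620 | 87% |

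The n column uses unrounded normal quantiles and the unrounded exposed rate. For comparison, the printed pair of rates, in either order, has 79% power at 5580.

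**The case against.** A reader might infer that the study is sized to show harm. The documents do not support that. The tests are two-sided and the formula is symmetric, so the design has the same power for a 1.3-point difference in either direction at these two rates. A label swap would leave recruitment, the test, the relative risk and the Cox analysis as they are.

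A reader might also infer that the sample size is too small. That holds under only one of the two assumed benefits in the table. Under the other, 6200 per group is more than enough.

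The assignment of 0.072 to the exposed group is itself an inference. Section 2.3 does not write that P1 is the exposed rate and does not name the event; the figure with the formula and the two cited sources cannot be seen. A reversed label is the simplest explanation.

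These points limit the consequence but do not remove the conflict. Word order and subscripts agree, nothing in the text points the other way, and a two-sided test does not supply a rationale for planning on the direction opposite to the aim. If the labels were held to be merely ambiguous, the same correction would be needed.

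**Conclusion.** The point holds as an inconsistency in the planning assumption. As printed, the expected effect is a risk ratio of 1.22 (+1.3 points) against Chinese patent medicine on an unfavourable outcome, while the stated aim is benefit. This rests on reading P1 as the exposed rate and on the rates referring to the main events; both readings are natural, but neither is spelled out.

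The effect on the sample size is nil if the labels are swapped. If 0.059 is the true nonexposed rate, power at 5580 per group is about 70% or 87% under the two assumed benefits, so the direction of the consequence is open until the benefit sought is stated. All these figures take two-sided alpha 0.05, and the sample sizes 80% power. That pair reproduces 5677; the printed Z values would require about 12,900 per group. This mismatch is a separate fault and changes the number far more than the labels do.

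**What to change.** Check both literature rates against the main-event definition in section 2.8.4 and the 48-week follow-up, then rewrite section 2.3 so that each rate carries its group, outcome and time window.

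- If the labels are swapped: write nonexposed P0 = 0.072 and exposed P1 = 0.059, risk ratio 0.82, for acute myocardial infarction, PCI or CABG by week 48. The cost is one sentence, and n does not change.
- If 0.059 is the nonexposed rate: state the benefit sought and the power that 6200 per group (5580 after 10% loss) gives for it. The cost is a restated power figure, and a revised sample size only if that power is judged too low.
- If the rates belong to another outcome or population: replace them with rates for the main events and recalculate.

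In the same paragraph, make the Z values agree with the sample size and with the alpha of 0.05 in section 2.11.2, because relabelling the rates alone would still leave 5677 unsupported by its printed inputs.

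### The 5677 per group does not follow from the printed Z values of 2.58 and 1.64, which need about 12,900; it matches 80% power at two-sided 5%

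*Protocol article*

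**What the plan says.** Section 2.3 (Sample size calculation) of the protocol article takes P1 = 0.072 and P0 = 0.059 from the literature and prints Z-alpha = 2.58 and Z-beta = 1.64. It then states: "Substituting the above values into the formula can be obtained, and the sample size of each group is about 5677 cases". The formula is in Figure 2, which is not shown in the text at hand. Neither the significance level nor the power is given in words.

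For attrition the section says "Control the rate of loss of follow-up within 10" per cent, and concludes: "There were about 6200 cases in each group, and the total sample size of this study was about 12,400".

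Section 2.11.2 (Main statistical analysis methods) sets the "efficacy comparison test level" at alpha = 0.05 and adds: "General statistical tests adopt bilateral tests".

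**The concern.** The text presents 5677 as the direct result of putting the printed values into the formula. Z = 2.58 is the two-sided 1% point and Z = 1.64 is the point for 95% power. A difference of 1.3 percentage points between two small incidences cannot be detected under error rates that strict with so few patients. Either the Z values or the sample size is wrong. The printed Z-alpha also disagrees with the 0.05 level in section 2.11.2.

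What is at stake is how the result will be read. Taken at face value, the Z values imply a 5% chance of missing the planned difference. If the true chance is about 20%, a null finding is much weaker evidence of no effect than the protocol suggests.

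**Working it through.** **Inputs.** From section 2.3: p1 = 0.072, p0 = 0.059, Z-alpha = 2.58, Z-beta = 1.64, n = 5677 per group, loss up to 10%, 6200 per group planned. From section 2.11.2: two-sided alpha 0.05.

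**Derived quantities.**
- d = 0.072 − 0.059 = 0.013, so d² = 0.000169.
- p1q1 + p0q0 = 0.066816 + 0.055519 = 0.122335, with square root 0.34976.
- Pooled p = 0.0655, so 2·p·q = 2 × 0.0655 × 0.9345 = 0.12242, with square root 0.34989.

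**Attempt to reproduce 5677 with the printed Z values.** The formula is n = [Zα·√(2pq) + Zβ·√(p1q1 + p0q0)]² / d².

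(2.58 × 0.34989 + 1.64 × 0.34976)² / 0.000169 = (1.47632)² / 0.000169 ≈ 12,897 per group.

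**The same formula with Z = 1.96 and 0.84.**

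(1.96 × 0.34989 + 0.84 × 0.34976)² / 0.000169 = (0.97958)² / 0.000169 ≈ 5677.9 per group.

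| Variance form | Z = 2.58, 1.64 | Z = 1.96, 0.84 |
|---|---|---|
| Pooled under the null, unpooled under the alternative | 12,897 | 5,678 |
| Unpooled throughout | 12,891 | 5,675 |
| Pooled throughout | 12,900 | 5,679 |

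The ratio is 12,897 / 5677 = 2.27, which is simply (4.22 / 2.80)².

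**Could the unseen formula explain the gap?** With 2.58 and 1.64, the other forms tried give:
- arcsine: 12,869
- continuity-corrected: 13,050
- event-based: 12,824 (Schoenfeld) and 12,908 (Freedman)
- reading alpha as one-sided 1% instead: 11,421

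Faulty forms do not reach 5677 either. Leaving out the factor 2 gives 6,450, and using p0q0 alone gives 5,850. Rounding of the incidences to three decimals does not help: over p1 from 0.0715 to 0.0725 and p0 from 0.0585 to 0.0595, n stays between 11,114 and 15,131.

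Other common Z pairs also miss: 2.58 with 0.84 gives 8,471, 1.96 with 1.64 gives 9,385, and 1.645 with 0.842 gives 4,479. Working backwards, 5677 implies a sum of Z values of 2.799, against 1.96 + 0.84 = 2.80 and 2.58 + 1.64 = 4.22.

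**Loss to follow-up.** 5677 / 0.90 = 6307.8, so 6308 per group are needed. The planned 6200 leave 6200 × 0.90 = 5580 at 10% loss. They absorb a loss of 1 − 5677/6200 = 8.4%.

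**Power for 0.072 against 0.059.**

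| Evaluable per group | Two-sided 0.05 | Two-sided 0.01 |
|---|---|---|
| 5580 (6200 less 10%) | 79.3% | 57.9% |
| 5677 | 79.9% | 58.9% |
| 6200 (no loss) | 83.3% | 63.7% |

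**The case against.** The arithmetic cannot be defended, but several points can be made for the plan.

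- **Error rates are inferred.** Section 2.3 never states 1% or 95% in words, and a sample size does not set alpha. Section 2.11.2 openly tests at 0.05, where power is about 80%, a conventional level. On this view the fault is a misreported planning assumption, not an underpowered study. This stands as to emphasis: 79% is the relevant figure for the planned test, and 58% applies only if testing were at 1%. It does not rescue the statement that the printed values give 5677.
- **The loss shortfall is small.** The 10% is a ceiling and 6200 is approximate; 6308 is 1.7% more. At the full 10% loss, power falls only from 79.9% to 79.3%. The planned Cox regression also lets patients contribute until they are lost. All of this stands, and alone the shortfall would be minor.
- **Intent is not documented.** The match with 1.96 and 0.84 is strong circumstantial evidence, not proof. If the sponsor meant 2.58 and 1.64, the sample size is the error. This is fair. Against it, 1.96 and 0.84 agree with both the printed sample size and the 0.05 level in section 2.11.2, while 2.58 and 1.64 agree with neither.

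**Conclusion.** The sample size statement is wrong as written. The printed Z values require about 12,900 per group, not 5677. The printed number corresponds to two-sided 5% and 80% power, and Z = 2.58 contradicts the analysis level of 0.05. With 6200 per group and 10% loss, the chance of missing the planned difference at the 5% level is about 21%, roughly four times the 5% that Z = 1.64 implies.

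This assumes equal groups, the stated incidences, a comparison of two proportions, and no information from patients lost to follow-up. Figure 2 could not be seen, but none of the forms tried turns 2.58 and 1.64 into 5677.

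**What to change.** Rewrite section 2.3 with two-sided alpha 0.05 (Z = 1.96), 80% power (Z = 0.84) and 5678 evaluable patients per group, and delete 2.58 and 1.64. State alpha and power in words, so that the planning level visibly matches section 2.11.2. For loss to follow-up, choose one of:

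- 5678 / 0.90 = 6309 per group, 12,618 in total; or
- keep 6200 per group (12,400 in total) and state about 79% power if 10% are lost.

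The second option is a change of wording only. The first adds 218 patients (12,618 − 12,400). Either way the stated power becomes less favourable than the 95% now implied.

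The sponsor should confirm that 5% and 80% were the intended error rates. If 1% and 95% were meant, the consequence is not wording: about 12,897 evaluable per group, or 12,897 / 0.90 = 14,330 per group and 28,660 in total, with the test level in section 2.11.2 changed to match.

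### The printed Z values (2.58 and 1.64) require about 12,900 patients per group, not 5677; the stated size gives about 80% power at two-sided 0.05, or 59% at the alpha that 2.58 implies

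*Protocol article*

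**What the plan says.** Section 2.3 (Sample size calculation) takes expected incidences from the literature, P1 = 0.072 for the exposed group and P0 = 0.059 for the nonexposed group. It gives Z_alpha = 2.58 and Z_beta = 1.64, describing them as quantities that "were the areas under the standard normal distribution, and the table was found to obtain" those values. It then reports the result: "Substituting the above values into the formula can be obtained, and the sample size of each group is about 5677 cases". After an allowance for 10% loss to follow-up, it concludes: "There were about 6200 cases in each group, and the total sample size of this study was about 12,400".

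The section states neither a significance level nor a power in words, so the two Z values are its only statement of the design's error rates.

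Section 2.11.2 (Main statistical analysis methods, item 6) sets the "efficacy comparison test level *α* = 0.05 between groups" and adds that "General statistical tests adopt bilateral tests".

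**The concern.** The section prints every input and says the result follows from them, so it can be checked directly. It fails by more than a factor of two. A Z_alpha of 2.58 is the two-sided 1% deviate and a Z_beta of 1.64 corresponds to 95% power. A study of 5677 per group cannot deliver both for a difference of 1.3 percentage points at these rates.

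There is a second conflict. The analysis section tests at two-sided 0.05, for which the deviate is 1.96, not 2.58.

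At stake is how the main result will be read. Someone who relies on section 2.3 would take the chance of missing a true 1.3-point difference to be 5%. It is about 20% at the level the study plans to use, and about 41% at the level implied by 2.58. A null comparison of the main cardiovascular events would then look more informative than it is.

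A smaller wording error is that the Z values are called areas under the normal curve. They are normal deviates; an area cannot exceed 1.

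**Working it through.** **Inputs.** From section 2.3: p1 = 0.072, p0 = 0.059, difference d = 0.013, Z_alpha = 2.58, Z_beta = 1.64, 1:1 groups, stated n = 5677 per group, 10% loss, 6200 per group recruited. From section 2.11.2: efficacy test at two-sided 0.05.

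**Formula.** Two proportions, equal groups, with pbar = (0.072 + 0.059)/2 = 0.0655:

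n = [Z_alpha·√(2·pbar·qbar) + Z_beta·√(p1q1 + p0q0)]² / d²

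- √(2 × 0.0655 × 0.9345) = √0.12242 = 0.34989
- √(0.072 × 0.928 + 0.059 × 0.941) = √0.12234 = 0.34976
- d² = 0.000169

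**Trying to reproduce 5677 from the printed Z values.**

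2.58 × 0.34989 + 1.64 × 0.34976 = 0.9027 + 0.5736 = 1.4763; squared, 2.1795; divided by 0.000169, **12,897 per group**. The printed figure is not reproduced: 12,897/5677 = 2.27.

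**Does the choice of formula explain it?** Figure 2, which holds the formula, was not available for this check, so the standard alternatives were run with 2.58 and 1.64:

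| Form | n per group |
|---|---|
| Pooled variance | 12,897 |
| Unpooled variance | 12,891 |
| Average proportion throughout | 12,900 |
| Continuity-corrected | 13,050 |
| Arcsine | 12,870 |
| Log relative risk | 12,952 |

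Reading alpha as one-sided 0.01 with 95% power gives 11,421. Even an incorrect form that counts only one group's variance gives 5850 (using p0), 6450 (using pbar) or 7041 (using p1), not 5677.

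**Which Z values do give 5677?** Pooled formula, same rates:

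| Z_alpha | Z_beta | Meaning | n per group |
|---|---|---|---|
| 1.96 | 0.84 | two-sided 0.05, 80% power | 5677.9 |
| 1.96 | 1.28 | two-sided 0.05, 90% power | 7602 |
| 1.96 | 1.64 | two-sided 0.05, 95% power | 9385 |
| 2.58 | 1.64 | two-sided 0.01, 95% power | 12,897 |

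The first row in full: 1.96 × 0.34989 + 0.84 × 0.34976 = 0.6858 + 0.2938 = 0.9796; squared, 0.95957; divided by 0.000169, 5677.9.

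**Power with 5677 per group.** Power = Φ[(d√n − Z_alpha × 0.34989)/0.34976], with d√n = 0.013 × 75.35 = 0.9795.

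- Z_alpha = 2.58: (0.9795 − 0.9027)/0.34976 = 0.220, power **59%**
- Z_alpha = 1.96: (0.9795 − 0.6858)/0.34976 = 0.840, power **80%**

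**Difference covered.** With 2.58 and 1.64, 5677 per group covers a difference of about 2.0 points from 5.9%, not 1.3.

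**Loss allowance.** 12,897/0.9 = 14,330 per group, or 28,660 in total, for the printed Z values. For the printed size, 5677/0.9 = 6308, slightly more than the 6200 stated. If 10% of 6200 are lost, 5580 remain, and power is 79% at two-sided 0.05 and 58% at two-sided 0.01.

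**The case against.** The best defence is that the sample size is right and only the Z values are misprinted. The value 5677 matches two-sided 0.05 and 80% power almost exactly, and two-sided 0.05 is the only significance level the article gives in words for efficacy. On that reading the study is conventionally sized, nobody intended alpha 0.01, and the 59% power and the 28,660 total describe a design that was never planned. It can also be said that no power is claimed in words, so 95% is inferred rather than asserted.

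Much of this is fair, and it governs how the size of the problem should be put. The 59% applies only at the alpha implied by 2.58; at the planned test level the figure is about 80%. The misprint reading is the more likely one, though the article does not show which element is wrong.

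The contradiction remains. Section 2.3 says that these particular Z values were substituted and produced 5677, and they do not. Either the Z values are wrong, and the power is 80% rather than the 95% they imply, or the size is less than half of what they require. The unseen formula does not help, because the standard forms differ by about 1% and the gap is 2.27-fold.

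**Conclusion.** The point holds. The printed inputs require about 12,897 per group; 5677 is 44% of that. At the stated rates of 7.2% and 5.9%, 5677 per group gives about 80% power at two-sided 0.05 and about 59% at two-sided 0.01, against the 95% that Z_beta = 1.64 implies. The printed Z_alpha also contradicts the test level in section 2.11.2.

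This rests on a standard two-proportion comparison with equal groups and on reading 2.58 as the two-sided 1% deviate and 1.64 as the deviate for 95% power. It must be corrected, because this calculation is the only justification given for the size of the study.

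**What to change.** In section 2.3, replace the two Z values with Z_alpha = 1.96 (two-sided alpha = 0.05) and Z_beta = 0.84 (80% power). Call them standard normal deviates, and state that the study has about 80% power at the two-sided 0.05 level of section 2.11.2 to detect 7.2% against 5.9%. Nothing should remain that implies alpha 0.01 or 95% power. The total of about 12,400 can stay. In the same edit, note that dividing 5677 by 0.9 gives 6308 per group, so 6200 leaves about 79% power if the full 10% are lost.

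The cost is one corrected sentence and a lower but true power statement, with no extra patients.

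If the sponsor did intend alpha 0.01 and 95% power, the size must instead be recomputed to about 12,900 per group (about 14,330 after the loss allowance), and section 2.11.2 changed to test at 0.01.
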